# Suprachoroidal VIsco-bucKlING versus gas tamponade for the treatment of rhegmatogenous retinal detachment (VIKING): study protocol for a multi-centre, randomised, controlled feasibility study

**DOI:** 10.1186/s40814-026-01787-w

**Published:** 2026-03-17

**Keywords:** Retinal detachment, Surgery, Vitrectomy, Suprachoroidal viscobuckling, Gas tamponade, Recovery, Feasibility, Randomised controlled trial

## Abstract

**Background:**

Rhegmatogenous retinal detachment (RRD) is a potentially blinding condition that affects ~ 1 in 10,000 adults per year. Retinal detachment surgery usually involves internal reapposition of the retina using the injection of a gas tamponade into the vitreous cavity. However, this has downsides including delayed visual recovery, the need to posture postoperatively, limiting fundal view during postoperative monitoring, and the risk of raised intraocular pressure. We examine a novel surgical variation, using a temporary suprachoroidal viscobuckle (SCVB) instead of gas. SCVB involves the controlled injection of high viscosity viscoelastic through an external scleral incision into the suprachoroidal space to create an indent under a causative retinal break. The sodium hyaluronate viscoelastic is resorbed over 2–3 weeks, long enough for intraoperative laser retinopexy to cause chorioretinal adhesion. The primary objective of this study is to establish if it is feasible to recruit, retain, and evaluate patients with RRD into a larger randomised controlled trial of SCVB. Secondary objectives are to make a preliminary assessment of safety and efficacy.

**Methods:**

This multicentre, randomised, controlled, two-group, unmasked feasibility trial recruits participants with primary RRD and a break or breaks within 1 clock hour. The CE-marked sodium hyaluronate viscobuckle is created during otherwise standard pars plana vitrectomy RRD surgery. Feasibility outcomes include screen failure rate, rate of recruitment, protocol compliance, and participant retention. The main efficacy outcome is retinal attachment with no intravitreal tamponade present and no subretinal fluid which could spread, without the need for further surgery, at week 12. The key secondary efficacy outcome is Early Treatment of Diabetic Retinopathy Study best-corrected visual acuity at week 24. Safety is recorded through adverse events and serious adverse events.

**Discussion:**

SCVB has multiple potential advantages for patients. This study will help determine if a definitive study of SCVB is justified and deliverable and inform its design.

**Trial registration:**

ClinicalTrials.gov Identifier: NCT04557527, registered 09 September 2020.

**Supplementary Information:**

The online version contains supplementary material available at 10.1186/s40814-026-01787-w.

## Background {6a, 6b}

Rhegmatogenous retinal detachment (RRD) is a potentially blinding condition that occurs when a break in the neurosensory retina allows vitreous fluid to pass into the subretinal space, lifting the neuroretina off the underlying retinal pigment epithelium (RPE). This typically causes a corresponding visual field defect that expands over time to involve the fovea, with loss of central vision. RRD affects ~ 1 in 10,000 adults per year in the United Kingdom (UK) and is the most common indication for retinal surgery [1–3]. Most RRDs require surgical repair, with the most common operation in the UK being vitrectomy, cryotherapy (cryo), or laser retinopexy and intravitreal gas tamponade; the next most frequent is scleral buckling, then combined vitrectomy with scleral buckling [2]. The primary reattachment rate following surgery has been reported as 80–90% [1, 2, 4].

The use of intravitreal expansile gases in RRD repair is burdensome for patients due to the need for head posturing (to maximise tamponade effect across the break) and severely reduces vision whilst the gas fills the eye. The gases take about 2–8 weeks to absorb; during this time, patients cannot fly, are advised not to drive, and must not have general anaesthesia using nitrous oxide which can cause gas expansion. Gases may increase the likelihood of post-vitrectomy cataract and postoperative intraocular pressure (IOP) elevation. Gases obscure the fundal view, making post-operative retinal examination and monitoring difficult.

Scleral buckling is one of the oldest recognised surgical procedures for the treatment of RRD [5]. It involves the suturing of a silicone explant onto the sclera to produce an indentation over the detached retina and retinal breaks [6]. This promotes retinal reattachment when combined with retinopexy to seal the break via a chorioretinal adhesion. Difficult surgical techniques, prolonged recovery and associated complications, i.e. injury to the extraocular muscles and diplopia, distortion of the globe and refractive change, ocular ischaemic syndrome, and exposure of the implant, have meant that surgeons have generally shifted away from this technique [2].

A technique that combines the advantages of vitrectomy and scleral buckling, without the burden of gas tamponade, could materially impact how vitreoretinal surgeons undertake the most commonly performed retinal operation [3].

Previous attempts to achieve gas-tamponade free retinal reattachment surgery have included the use of fibrin glue and meticulous laser [7–10], but neither has had widespread adoption.

This study investigates a variation to vitrectomy surgery, wherein a temporary suprachoroidal viscobuckle (SCVB) is used instead of gas tamponade. SCVB is a new technique that involves the controlled injection of viscoelastic into the suprachoroidal space to create an indent similar to scleral buckling under direct visualisation. High viscosity sodium hyaluronate ophthalmic viscosurgical device (OVD) has been safely used in the eye for this purpose and has a mean elimination time of 2 weeks, long enough for retinopexy to cause a chorioretinal adhesion [11]. Although the injection of sodium hyaluronate OVD into the suprachoroidal space to create a buckle effect is novel, it has a long history of intraocular use and is widely used as a surgical device in standard cataract surgery [12].

Compared to conventional scleral buckling with a silicone implant, SCVB offers a minimally invasive approach, with no manipulation of the extra-ocular muscles and potentially quicker recovery. Compared to vitrectomy, it avoids all the downsides of intravitreal gas tamponade.

Retrospective case series showeed good success and low complication rates with SCVB (REFS) [13–16]. Four case series of 14 to 62 patients (138 in total) report a primary retinal reattachment success rate between 92 and 100% [13–16], similar to reported reattachment rates of 80–90% [1, 2] with standard RRD surgical techniques. Complications were reported to be rare [14–17] and included single incidences of bleeding from the sclerotomy site, localised retinal or choroidal haemorrhage, retinal or choroidal trauma, transient elevation of IOP; none of which required further intervention.

To realise the potential patient benefits of SCVB surgery, we first need to establish that SCVB has an anatomic and visual outcome that is no worse than standard vitrectomy. That is likely to require a large, randomised, non-inferiority trial. Such a study will be expensive and is unlikely to attract Industry funding. We therefore need a robust feasibility study before we are able to apply to a government or charitable funder to undertake a definitive study.

The suprachoroidal viscobuckling versus gas tamponade for the treatment of rhegmatogenous retinal detachment (VIKING) trial aims to establish if a pivotal randomised controlled trial (RCT) is justified and deliverable and to inform its design.

### Trial design {8}

VIKING is a multicentre, two-group, randomised, if the surgical device is non-masked device feasibility trial.

### Objectives {7}

This study is designed to determine if a larger, efficacy study is justified and deliverable, and to inform the design of any such study. A subsequent study is likely to have a non-inferiority design, wherein the primary hypothesis is that the patient advantages of SCVB (no gas tamponade and possibly fewer cataracts) can be realised without a worse anatomic or visual outcome.

The primary objective is to establish if it is feasible to recruit, retain, and evaluate patients with RD into a larger randomised controlled trial of SCVB.

Secondary objectives are to make a preliminary assessment of the safety and efficacy of SCVB.

## Methods: participants, intervention, outcomes

VIKING is reported in line with the CONSORT 2010 extended guidelines for randomised pilot and feasibility trials [18], and the protocol has been developed in line with SPIRIT guidelines [19]. A SPIRIT figure is included in Table 3 in the Appendix (as the schedule of assessments), and the SPIRIT checklist is included in the supplementary appendix (Appendix A). The trial sponsors are King's College London and King's College Hospital (Clinical Co-Sponsor).

### Setting {9}

VIKING aims to recruit 50 participants over 2 years from six NHS hospitals. A multi-centre approach will improve the likelihood of recruiting to target in the desired time frame, but also to ensure participants are drawn from a broader population than afforded by a single study site.

### Consent {11b, 26a}

Written informed consent will be obtained by a site’s principal investigator (PI) or delegated sub-investigator (SI) before any study procedures are undertaken, including screening. Patients will be recruited from the day of presentation and will be given 24–72 h to make the decision whilst awaiting urgent surgery. The short consent period is required due to the need for urgent surgery in most cases. Nonetheless, we anticipate that most patients will be able to take the information sheet home overnight, with time to discuss its contents with friends and family if desired. They can hold off joining the study right up to the point of surgery, to give as much time as possible to consider the options. Conversely, participants who have already enrolled will be made aware that they can withdraw from the study right up until the point of surgery and their consent will be reconfirmed during the pre-operative ward round (they can of course withdraw after surgery, but by then they may have already received SCVB). RRD surgery has an appreciable failure rate of about 10–20% [1, 20]. It is possible that patients may attribute any surgical complications or surgical failure to SCVB when these were anyway inherent to RRD surgery. Careful explanation will be provided to communicate that SCVB may not change the surgical outcome but is aimed at improving the recovery time after surgery. The general risks of surgery will be detailed in the patient information sheet, separately to those thought possible due to the altered surgical step (SCVB instead of gas).

#### Eligibility criteria

##### Inclusion criteria

Males and females aged at least 18 years (including females of childbearing age) requiring pars plana vitrectomy for the treatment of primary RRD caused by a single break or multiple breaks within one clock hour. The final determination of qualifying breaks is made at the time of surgery following 360-degree internal indented search using a wide-angle viewing system.

##### Exclusion criteria

General:Hypersensitivity to sodium hyaluronate OVD.Participation in another interventional study within 8 weeks of enrolment or planned to occur during this study.Bleeding disorders or the use of anticoagulants (such as warfarin, rivaroxaban) or dual anti-platelet drugs such as aspirin with clopidogrel. Monotherapy with low dose (≤ 100 mg) aspirin is permitted, and if clinically appropriate this should be stopped prior to surgery and recommenced only after satisfactory day 1 postoperative review.Unwilling, unable, or unlikely to return for scheduled follow-up for the duration of the trial.Any other condition that, in the opinion of the investigator, would prevent the participant from granting informed consent or complying with the protocol, such as dementia, mental illness, or serious systemic medical disease.

Study eye:Presence of proliferative vitreoretinopathy (PVR) or any tractional RD.Previous vitreoretinal surgery, open-globe injury, or endophthalmitis.Aphakia.Congenital cataract.Previous or current suprachoroidal haemorrhage.Congenital or acquired ocular, orbital or periocular abnormality that, in the opinion of the attending vitreoretinal surgeon, would preclude the safe delivery of the OVD into the suprachoroidal space.Presence of other ocular comorbidity that, in the opinion of the investigator, is likely to prevent an accurate assessment of retinal attachment.Current intraocular inflammation other than mild cellular activity that is thought to be secondary to RRD.Current ocular or periocular infection other than blepharitis.

The reasons for ineligibility or withdrawal will be recorded and described.

#### Intervention

This RCT is comprised of 2 arms:Control arm—participants undergo standard vitrectomy, cryo or laser retinopexy, and gas procedure. The choice of gas (SF_6_, C_2_F_6_, or C_3_F_8_) is determined by the surgeon’s preference and position of the break. Participants are advised to posture postoperatively, dependent on the position of the break.Study arm—vitrectomy, SCVB, and laser retinopexy procedure.

The SCVB surgical technique involves a small incision in the sclera, 5–6 mm behind the limbus in the clock hour of the break, to access the suprachoroidal space. A small amount of viscoelastic is injected to bluntly dissect choroid from the sclera. These structures are opposed rather than attached to each other; therefore, very little resistance is felt when opening this potential space. The SCVB is created under direct visualisation by the surgeon injecting the viscoelastic while adjusting the direction of the cannula directly under the break. The height of the indent should be sufficient to cover the perimeter of the break. The breaks are treated with laser retinopexy after creation of the indent. Air tamponade is allowed if the surgeon deems it necessary, but that does not mandate posturing and will absorb much quicker than gas tamponade. The suprachoroidal buckling procedure may be abandoned in favour of standard of care if a complication took place, i.e. clinically significant choroidal or retinal injury or significant haemorrhage, at the surgeon’s discretion.

The trial commenced using HEALON5™ PRO OVD (Johnson & Johnson Surgical Vision, Inc., Wokingham, UK). The Healon family of viscoelastics has been in use for over two decades, and we estimate that it has been used in millions of eye operations. We know of no clinical concerns about biocompatibility or toxicity. The HEALON5™ PRO OVD used in this trial is used within its marketing authorisation: ‘Sodium hyaluronate OVD can also be used to efficiently separate and control ocular tissues. It is not designed to have any pharmacological effect’ [21]. The protocol was amended to allow the use of two very similar products, OphteisBio (Rayner, Worthing, UK) and NuViscTM PRO (BVI Medical, Elland, UK), also used within their marketing authorisation.

### Concomitant care {11d}

All concomitant care determined necessary by site investigators is permitted for this study and will be recorded in case report forms. The time to and proportion of participants who experience a re-detachment in their study eye is an important outcome for this study; however, participants will not undergo repeat SCVB surgery if they experience a re-detachment. Standard of care vitrectomy surgery will be offered instead.

### Randomisation {16a, 16b, 16c}

Randomisation and allocation are performed in the operating theatre using the centralised web-based Castor electronic data capture (EDC) system (Amsterdam, Netherlands), after the internal search of the eye and exclusion of additional breaks in the detached retina. Those who were found to have additional breaks will be documented as screen failures. The PI or delegated SI will undertake randomisation, and all have been allocated logins to the VIKING study EDC. Allocation occurs on the web portal immediately and is 1:1 to either SCVB or comparator with no randomisation stratifiers.

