### Statistical analysis {14, 20a, 20b, 20c}

VIKING is not powered to test an efficacy-based hypothesis and no interim analysis is planned. The results will instead be descriptive, without any statistical comparisons. As noted in the section above, this study is not designed to test a hypothesis, but rather to inform a future study. We selected 25 participants for each arm, as that will give an estimate of visual acuity variance and may start to expose any difference in anatomic success rate [22, 23].

A total of 50 patients will provide a reasonable estimate of screening success, recruitment rate, retention, the ability to evaluate patients, attrition and time to ‘stress test’ the protocol, addressing the main feasibility outcomes of the study. With a sample size of 50 participants, we will be able to estimate the proportion of participants with an evaluable primary outcome of 80% with a 95% confidence interval of ± 11%.

From a feasibility perspective, we anticipate that a pivotal trial would be deliverable if the criteria detailed in Table 2 were met.

We recognise that the decision to proceed with a subsequent pivotal trial depends on an appreciation of the totality of the results, not just the feasibility metrics, including the apparent risks, benefits, estimated effect size, minimum clinically important difference, future unmet need, suitable funding streams, input from patient focus groups, amongst other factors (Table 2).

**Table 2 Tab2:** Feasibility thresholds for a future study

Feasibility metric	No-go	Protocol modifications	Proceed without change
Recruitment (patients per month per site)	< 0.1*	0.1–0.3	> 0.3
Evaluable primary outcome (combining attrition and otherwise missing primary outcome data)	80%	81–88%	> 88%

*A slowly recruiting trial may be justified if the sample size is deliverable, and the clinical impact warrants an extended recruitment timeline and/or a large number of sites

A description of baseline demographics and ocular characteristics will be provided by group to include age, sex, best-corrected visual acuity (BCVA), laterality, lens status, location, and number of retinal breaks, and RD location.

The efficacy population will be ‘intent-to-treat’, including all randomised participants, but a ‘per protocol’ analysis will include all those randomised to SCVB who received it, and all those randomised to standard vitrectomy who received it.

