For continuous efficacy variables, we plan to report the mean and standard deviation, unless the data appear skewed, in which case we will consider reporting the median and interquartile range. For categorical values, we will report proportions, with 95% confidence intervals.

In addition to the main BCVA results, BCVA will be reported in the subgroups of eyes that are phakic and pseudophakic, and those with macular-on and macular-off RDs, since post-vitrectomy cataract and macular status can materially influence BCVA outcomes.

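### Allocation is not stratified by macular status and the main week-24 BCVA results are crude arm means, so chance imbalance adds avoidable noise to the acuity comparison; a standardised estimate would remove most of it

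*Protocol article*

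**What the plan says.** Protocol article, Randomisation: eyes are allocated in theatre through a central web system, after the internal search. "Allocation occurs on the web portal immediately and is 1:1 to either SCVB or comparator with no randomisation stratifiers".

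Protocol article, Statistical analysis, on sample size and type of analysis: "We selected 25 participants for each arm, as that will give an estimate of visual acuity variance". Also: "VIKING is not powered to test an efficacy-based hypothesis and no interim analysis is planned", and "The results will instead be descriptive, without any statistical comparisons".

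The same section, on acuity: beyond the main results, "BCVA will be reported in the subgroups of eyes that are phakic and pseudophakic, and those with macular-on and macular-off RDs", the reason given being "since post-vitrectomy cataract and macular status can materially influence BCVA outcomes". BCVA at week 24 is the key secondary efficacy outcome (Abstract and the summary table in the Appendix).

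The same section, on use of the results: the decision on a pivotal trial rests on many considerations beyond the feasibility metrics, "including the apparent risks, benefits, estimated effect size, minimum clinically important difference" among them.

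The list of baseline characteristics to be described by group includes BCVA, lens status and RD location. Macular status is not named as such.

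**The concern.** The protocol identifies macular status as a strong determinant of its key secondary outcome, yet neither the allocation nor the main BCVA summary takes account of it. Macular status is a feature of the detachment that exists before the in-theatre allocation, so it could have been used.

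With 25 eyes per arm, one arm can by chance receive noticeably more macula-off eyes, and the crude arm means then differ for a reason unrelated to SCVB. Because the analysis is descriptive, nothing stated for the main results corrects for this, and the crude difference is the natural source of the estimated effect size carried into planning of a pivotal trial. The Objectives section expects that trial to be a non-inferiority trial on anatomic or visual outcome, where a few letters either way could colour the judgement.

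**Working it through.** **The plan's own precision figure.** For 80% evaluable with N = 50: 1.96 × √(0.8 × 0.2 / 50) = 0.111, which reproduces the stated ± 11%. It concerns feasibility and does not involve macular status.

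**Inputs.** From the protocol article: 25 eyes per arm, 1:1, no stratifiers. Assumed, because the article gives none: macula-off prevalence p = 30–50%; acuity gap between macula-on and macula-off eyes G = 10–20 letters; within-stratum SD σ = 10–20 letters; equal arms with all eyes evaluable.

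**Step 1: how likely is an imbalance?** Take the macula-off counts in the two arms as independent Binomial(25, p). A difference of 5 eyes is 5/25 = 20 points.

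| p | SD of difference in proportions, √(2p(1−p)/25) | P(≥ 5 eyes) | P(≥ 6 eyes) | P(≥ 8 eyes) |
|---|---|---|---|---|
| 0.3 | 0.130 | 0.164 | 0.088 | 0.020 |
| 0.4 | 0.139 | 0.193 | 0.111 | 0.029 |
| 0.5 | 0.141 | 0.203 | 0.119 | 0.033 |

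So a 20-point imbalance in macular status has a probability of about 16–20%. If lens status is counted as a second, independent factor of similar prevalence, the chance that at least one is off by 20 points is 1 − (1 − 0.164)² = 0.30 to 1 − (1 − 0.203)² = 0.36.

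Fixing the total number of macula-off eyes makes the answer depend on whether that total is odd or even. With exactly 25 of 50, the arm difference can only be odd and P(≥ 5) = 0.258. With 24 or 26 it can only be even and the figure is 0.156; with 20 it is 0.148. The averaged 16–20% is the fairer summary.

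**Step 2: what does it do to the acuity difference?** Shift = imbalance × G. For 20 points: 0.20 × 10 = 2 letters, 0.20 × 15 = 3, 0.20 × 20 = 4.

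**Step 3: compare with sampling error.** At p = 0.5 the total variance is σ² + 0.25G², and the 95% half-width of the crude arm difference is 1.96 × √(σ² + 0.25G²) × √(2/25).

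| σ | G | Crude half-width | Half-width with macular status balanced | Share of variance due to macular status | Shift at 20 points |
|---|---|---|---|---|---|
| 10 | 10 | 6.2 | 5.5 | 20% | 2 |
| 10 | 20 | 7.8 | 5.5 | 50% | 4 |
| 15 | 15 | 9.3 | 8.3 | 20% | 3 |
| 20 | 10 | 11.4 | 11.1 | 6% | 2 |
| 20 | 20 | 12.4 | 11.1 | 20% | 4 |

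The shift is smaller than the half-width throughout. The least favourable case is σ = 10, G = 20, where it is 4 against 7.8 letters, about half.

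**Step 4: what does standardising recover?** Take 60% v 40% macula-off, that is 15 and 10 eyes v 10 and 15. With each stratum weighted 0.5, the variance factor is 2 × 0.25 × (1/15 + 1/10) = 0.0833, against 2/25 = 0.08 under perfect balance. The ratio is 1.04, about 2% on the standard error. In the middle case (σ = G = 15) the half-width is 1.96 × 15 × √0.0833 = 8.5 letters, against 8.3 with perfect balance and 9.3 for the crude difference. Standardising after the fact thus recovers nearly all that stratified allocation would have given.

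**The case against.** Much can be said for the plan. Unstratified 1:1 allocation is valid and unbiased. The trial's purpose is feasibility, it is expressly not powered for efficacy, and it plans no comparison. The recruitment and evaluability thresholds do not depend on macular balance. The planned subgroup reports address the very factors at issue; if they are shown by arm with counts, a reader could form the standardised means from them. The estimated effect size is only one of several inputs, and no go/no-go rule turns on BCVA. All of this stands and keeps the point small.

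It can also be said that adjustment may be in an analysis plan that is not shown. That carries less weight: an analysis plan cannot alter the allocation, and the article itself settles on a descriptive analysis. The subgroup reports come in addition to the main results, which remain crude, and the article mentions no combined estimate.

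A reader might infer more: that chance imbalance could drive the apparent BCVA difference, that it biases the comparison, or that an SCVB effect could not be separated from it. The documents do not support this. The likely shift is within sampling error under every assumption tried, randomisation remains unbiased, and the planned subgroups allow at least a partial separation. Nor should the risk be put at 26% for one factor or 45% for either of two, since those figures belong to the odd-total case of exactly 25 macula-off eyes.

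**Conclusion.** The point holds as a modest, inexpensive improvement; it is not an error or a contradiction. Allocation ignores a factor that the protocol regards as influential, and the main BCVA means do not correct for it. A 20-point imbalance has a probability of about 16–20% and would move the crude difference by about 2–4 letters, against a half-width of about 6–12 letters. In the middle case, macular status carries about 20% of the variance of the crude difference, and that share is avoidable.

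The prevalence, the acuity gap and the SDs are assumptions; fewer evaluable eyes at week 24 would widen the half-width. The feasibility outcomes, their thresholds and the sample size are unaffected.

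**What to change.** For VIKING: add macular status by arm to the baseline table, and report, beside the raw week-24 BCVA means, arm means standardised to the pooled macula-on/off distribution. Within each arm this is the weighted average of the two stratum means, with the pooled proportions as weights. It needs no test, so it fits the descriptive plan, and it uses a factor that the subgroup reports already require. The cost is one baseline row and one row in the BCVA table. Since the Trial status section says the trial has completed, label the estimate as added afterwards unless the analysis plan already contains it. Standardise to macular status at baseline and not to cataract after surgery, which the Objectives section expects the treatment itself may affect.

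For the pivotal trial: consider macular status as a stratifier. The cost is one yes/no field on the web form and some predictability within blocks, which central allocation across sites limits. VIKING's own allocation cannot now be changed.
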